### Recruitment and enrolment procedures

A list of eligible infants was extracted from the ‘Exposed Infant Registers’, comprising the name of the biological mother, village, name of the child, date of birth of the child, ART number of the mother and contact details. For the 30 trial clinics there were a total of 1509 eligible infants extracted from the health facility PMTCT registers. Case care workers (CCW) in catchment areas of villages with the highest number of clinics were asked to invite all eligible caregiver-child dyads who met the trial inclusion criteria (*n* = 671) to attend an orientation meeting to learn about the trial. If the biological mother listed in the register was no longer the primary caregiver, the non-biological caregiver was invited to participate as long as the child was listed as HIV exposed. Eligible caregivers who provided verbal consent to participate were booked for enrolment procedures – *n* = 574 and 97 (14.5%) declined enrolment. Enrolment in the CHIDO intervention and usual care arms occurred concurrently, with one clinic from each arm recruited at a time for implementation purposes. Enrolment took 6 months to complete. Follow up for each pair of clinics was 12 months after the CHIDO intervention arm has started receiving the intervention in their community.

All eligible caregiver-child dyads were given trial information and asked to provide written informed consent to participate. Informed consent was collected according to Good Clinical Practice guidelines.

Table 1 summarises the scheduled trial timeline, from participants’ enrolment, intervention roll out, follow up assessments to data analysis phase.

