### Randomisation process

The imbalance between arms was minimised by using restricted randomization, minimising on the number of HIV exposed infants between 0 and 24 months per clinic. Mapping of all clinic clusters within the two districts was conducted before recruitment and enrolment in each district. Of all the mapped clinics, those with fewer than 30 annual deliveries were excluded from the randomization process. The remaining 30 clusters were randomly allocated to the intervention versus usual care arms. The intervention was delivered to groups of 12 dyads, and 6 health facilities of sufficient size to run one group and 9 facilities of sufficient size to run two groups were allocated to each arm (Fig. 2). To maximise transparency and buy-in from key stakeholders, a public randomisation procedure was undertaken (in January 2016 in the first district and in May 2016 in the second district) involving MOHCC, and district level governance and medical representatives.

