### Data analysis

Given the small number of clusters in the trial, cluster-level summary methods will be used. Analysis will be intention-to-treat. Age standardised ELC scores will be calculated from a combination of scores in the four cognitive domains of the Mullen Scales at endline using a HIV negative population in this setting, or a USA reference population if a local reference population cannot be obtained. The mean age-standardised composite score for each cluster will be estimated and the difference in means between arms calculated. The 95% CI for the mean difference will be estimated using a stratified t-test, with variance estimated from the residual mean square from an analysis of variance of cluster-specific means on stratum and trial arm. Analysis will adjust as fixed effects for baseline ELC score, stratum, and the following factors if they are imbalanced between arms at enrolment: age of children and caregivers, HIV status of children, socio-economic status and caregivers’ mental health. For the HIV-specific primary outcomes (proportion of children retained in care at 12 months and proportion with unsuppressed viral load) and for binary secondary outcomes, the unadjusted prevalence ratio will be estimated as the ratio of the geometric mean percentage in the intervention cluster versus the control cluster and compared using logistic regression. The main analysis will be complete case, with multiple imputation as a sensitivity analysis for the two primary outcomes, using variables associated with the outcome and with missingness. Further sensitivity analysis will use individual-level logistic regression and compare the result with the cluster-level methods described above.

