### Trial status

At the time of the manuscript submission, recruitment for the trial was completed and process evaluation and data analysis ongoing.

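### Five baseline factors enter the primary ELC analysis only if they look imbalanced between arms; they should be fixed in advance for prognostic value

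*Protocol article*

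**What the plan says.** The Data analysis section of the protocol article chooses cluster-level summary methods for the ELC score. The confidence interval for the difference in means has its "variance estimated from the residual mean square from an analysis of variance of cluster-specific means on stratum and trial arm". The section then turns to adjustment: "Analysis will adjust as fixed effects for baseline ELC score, stratum, and the following factors if they are imbalanced between arms at enrolment". That sentence has two parts.

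- Always included: baseline ELC score and stratum.
- Conditionally included: "age of children and caregivers, HIV status of children, socio-economic status" and caregiver mental health, which makes five factors.

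No other section fixes the covariate set. The section does not say whether the stratified result or the adjusted one is the primary estimate. According to Trial design and Randomisation process, the restricted randomisation balanced only the number of HIV-exposed infants per clinic, which is none of the five.

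**The concern.** A covariate earns its place in a trial analysis by predicting the outcome. Balance between arms is a separate matter. A strongly prognostic factor is worth adjusting for even when its means agree across arms, because it removes residual variance. A factor unrelated to the outcome adds nothing even when its means differ. The stated rule selects on balance alone, so it can drop the first kind and admit the second.

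It also leaves the primary model open until baseline data by arm have been examined. Defining a threshold for imbalance elsewhere would make the rule mechanical, but the criterion would still be the wrong one. At stake is precision in a trial of 30 clusters, and a primary model that is known only after the data are seen.

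**Working it through.** **The plan's own figure.** Inputs from Sample size: mean 110.6, SD 16.1, k = 0.15, 16 dyads per cluster, 20% loss, effect 1.23 SD. Two-sided alpha of 0.05 is assumed from the 95% interval.

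- m = 16 × 0.8 = 12.8; d = 1.23 × 16.1 = 19.80; second mean = 130.4.
- c = 1 + (1.96 + 0.84)² × [2 × 16.1²/12.8 + 0.15² × (110.6² + 130.4²)]/19.80²
- c = 1 + 7.85 × (40.5 + 657.8)/392.2 = 14.98, so 15 clusters per arm.

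The stated figure reproduces. It assumes no covariate adjustment, so nothing here changes it.

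**How open the model is.** Five in-or-out factors allow 2⁵ = 32 models. If a factor is called imbalanced at p < a and the factors are independent (both assumed), the chance that at least one enters is 1 − (1 − a)⁵:

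- a = 0.05: 23%
- a = 0.10: 41%
- a = 0.20: 67%

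**What the rule does to the test.** This was simulated with 15 clusters per arm, two strata of 6 and 9 clinics per arm (from Randomisation process), and baseline ELC and stratum always in the model. The five independent factors were entered at cluster level, with 6,000 runs per scenario. The unit is the SD of cluster means left after baseline ELC and stratum; power is for an effect of 1 such SD. For scale, the plan's own inputs give a cluster-mean SD of √(698.3/2) = 18.7, so its target effect is 19.80/18.7 = 1.06 SD before any adjustment. Ranges cover imbalance thresholds of p < 0.05 and p < 0.20. The share of variance explained is assumed.

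| Variance explained by the five | Rule | True SE | Type I error | Power |
|---|---|---|---|---|
| 20% | never adjust | 0.37 | 4.8% | 73% |
| 20% | always adjust | 0.36–0.38 | 4.6–5.2% | 73% |
| 20% | only if imbalanced | 0.37–0.38 | 4.4% | 70–72% |
| 50% | never adjust | 0.37 | 4.6–5.0% | 73% |
| 50% | always adjust | 0.29–0.30 | 4.3–5.1% | 89–90% |
| 50% | only if imbalanced | 0.33–0.36 | 2.8–3.5% | 72–75% |

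Monte Carlo error is about 0.3 points at 5% (√(0.05 × 0.95/6000)) and 0.6 points at 73% power.

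The conditional test is conservative because its reported SE is too large. At 50% explained variance the reported SE is about 0.38, against a true SE of 0.33 to 0.36.

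**Why fixed adjustment gains nothing at 20%.** Before the five factors there are 30 − 4 = 26 residual degrees of freedom (intercept, arm, stratum and baseline ELC removed). Five cluster-level terms leave 21. For random covariates the expected variance rises by (26 − 1)/(21 − 1) = 1.25.

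- At 20%: 0.80 × 1.25 = 1.00, so no net gain.
- At 50%: 0.50 × 1.25 = 0.625, and 0.372 × √0.625 = 0.294, which agrees with the simulation.

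How the covariates are entered therefore matters as well as which ones are chosen.

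**The case against.** The strongest reply is that the rule is mild. The candidate list is pre-specified, and the rule looks at enrolment data rather than outcomes. Baseline ELC, probably the strongest predictor, is always in. With baseline ELC included and the score already age-standardised, 50% explained variance may well be generous. HIV status may add little: at the transmission rates of 6.39% and 6.7% cited in Background, a 16-dyad cluster would hold about one infected child (16 × 0.0639 = 1.02; 16 × 0.067 = 1.07), if those rates apply here. All of this stands, and it limits the size of the point. It does not make balance the right criterion.

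A reader might also infer more than the article supports:

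- **That all adjustment is conditional.** It is not; only the five factors are.
- **That 32 possible models inflate type I error.** Applied mechanically, the rule does not. Discretion in calling a factor imbalanced is a separate risk, but a threshold is something an analysis plan may well supply, so its absence here is no finding.
- **That imbalance came from selective recruitment.** Allocation was public ("a public randomisation procedure was undertaken (in January 2016 in the first district and in May 2016 in the second district"), and case care workers were "asked to invite all eligible caregiver-child dyads who met the trial inclusion criteria". That makes selection possible; nothing shows that it occurred. If it did, adjusting for what is imbalanced would have some rationale, though a fixed prognostic set would cover the listed factors too.
- **That the model was being chosen with outcomes by arm in view.** Trial status says only "recruitment for the trial was completed and process evaluation and data analysis ongoing", and Data analysis is written in the future tense.
- **That retention receives no adjusted analysis.** The article says how an unadjusted ratio is computed. It does not say that this is the only analysis.

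**Conclusion.** The point holds at moderate weight. The protocol states a selection rule for five covariates that rests on the wrong criterion and leaves the primary ELC model unsettled until baseline data by arm are seen. The consequence is lost precision and a somewhat conservative test, with simulated type I error between 2.8% and 4.4%.

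Against fixed adjustment the power loss is about 1 to 3 points if the five factors explain 20% of the remaining cluster-level variance, and about 15 to 17 points if they explain 50%. Both shares are assumptions; the article gives no figure for them. The results also assume independent factors, cluster-level entry and thresholds of p < 0.05 or p < 0.20. The sample size and stated power are unaffected.

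**What to change.** Delete the condition on imbalance. Working blind to outcome by arm, and with a dated record, fix one covariate set for the ELC analysis: baseline ELC, stratum, and those of the five listed factors chosen for prognostic value. If any of the five is left out, such as caregiver age, give the reason.

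Apply the set in two stages. First regress the individual ELC scores on the covariates without arm. Then compare cluster mean residuals between arms with the stratified t-test. This keeps the cluster degrees of freedom (30 − 2 − 1 = 27 with two strata, assumed) instead of spending five of them on cluster-level terms. The two-stage version was not itself simulated. Name the adjusted estimate as primary and report the unadjusted stratified result beside it.

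The cost is small but not nil. The change comes late, and under Protocol modification it must be communicated to partners and funders and entered in the registry. Because the main analysis is complete case, a simple rule for missing baseline covariates, applied without regard to arm, is needed so that compulsory covariates do not shrink the analysed set. The questionnaire domains under Data collection cover these factors, so no new data should be needed.

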### Data collection

During the enrolment visit, all participating caregiver-child dyads were allocated a unique identifier to ensure patient confidentiality. Baseline data were collected using an interviewer-administered questionnaire and Audio Computer Assisted Survey Instrument (ACASI) for the sensitive parts of the questionnaire administered with the caregiver and a developmental assessment of the child. Caregivers received guidance on using ACASI from trained surveyors with regards to using the laptop and headphones to listen to instructions, questions, and responses that have been digitally recorded onto the ACASI platform.

The questionnaires collected information on the following domains: demographic characteristics, household characteristics, income and expenditure, food security, antenatal, delivery and post-natal care related to birth of participating child, infant and child feeding practices, maternal mental health, parental stress, HIV testing, disclosure and treatment history for self and participating child, self-reported ART adherence. Questionnaire data were entered directly onto tablets pre-programmed using Open Data Kit with range and consistency checks incorporated.

A follow up assessment was conducted among enrolled caregiver-child dyads after 12 months of programme implementation. This assessment was conducted in the same order in which the clusters were enrolled. Caregivers completed the follow up questionnaire administered in the same way as at baseline. Children had a full developmental assessment conducted by a trained assessor.

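### Any secondary outcome analysed as binary and also measured at baseline is given only an unadjusted prevalence ratio, which is valid but ignores a baseline value already collected

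*Protocol article*

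**What the plan says.** All from the protocol article.

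- **Binary secondary outcomes (Data analysis).** The estimate named is unadjusted: "for binary secondary outcomes, the unadjusted prevalence ratio will be estimated". It is formed from geometric means of the cluster percentages. The arms are then compared by logistic regression, for which no covariates are listed.
- **ELC (same paragraph).** "Analysis will adjust as fixed effects for baseline ELC score, stratum, and the following factors if they are imbalanced between arms at enrolment". The factors that follow include caregivers' mental health.
- **Sensitivity analysis (same paragraph).** "Further sensitivity analysis will use individual-level logistic regression and compare the result with the cluster-level methods described above". Again no covariates are named.
- **What is measured and when (Data collection).** The questionnaire domains include "maternal mental health, parental stress, HIV testing, disclosure and treatment history for self and participating child, self-reported ART adherence", and food security stands in the same list. At 12 months, "Caregivers completed the follow up questionnaire administered in the same way as at baseline".
- **Secondary outcomes (Table 2).** These include the Edinburgh Postnatal Depression Scale, the SSQ-8, a household hunger scale and the MARS. No cut-offs are given, and the article does not say which of them will be analysed as binary.

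**The concern.** The plan accepts, for ELC, that an outcome measured at both visits should be adjusted for its baseline value. For binary secondary outcomes it names the unadjusted estimate and gives no reason for the difference. Depending on which scales are dichotomised, this could affect common mental disorder, postnatal depression, household hunger and self-reported adherence.

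Two things are at stake. The first is precision: where the state partly persists over 12 months, the baseline value explains some of the endline variation, and an unadjusted interval is wider than it need be. The second is baseline difference between arms. There are 15 clinics per arm, and allocation was restricted only on the number of HIV-exposed infants, so nothing balances depression, hunger or adherence. A difference could arise by chance. It could also arise through differential recruitment, if dyads enrolled knowing their arm. Randomisation was public and participants were not blinded at baseline, but the article does not date enrolment against randomisation clinic by clinic, so that route is conditional. The Discussion anticipates better household food security; if that outcome is dichotomised, the claim would rest on this estimate.

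**Working it through.** **1. The plan's own figure.** Sample size inputs: 15 clusters per arm; 16 dyads enrolled per cluster with 20% loss, so 16 × 0.8 = 12.8 analysed; retention 65% in control and a 20-point difference, so 85%; k = 0.2. Two-sided alpha of 0.05 is assumed. The variance of a cluster proportion is p(1−p)/12.8 + (0.2p)².

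| Arm | Within-cluster | Between-cluster | Total |
|---|---|---|---|
| 65% | 0.0178 | 0.0169 | 0.0347 |
| 85% | 0.0100 | 0.0289 | 0.0389 |
| Sum | 0.0277 | 0.0458 | 0.0735 |

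The standard error of the difference is √(0.0735/15) = 0.0700, and 0.20/0.0700 = 2.86. Power from the noncentral t with 28 df is 78.7%. The normal approximation gives 81.5% with 15 clusters per arm and 78.8% with 15 − 1 = 14. The stated 80% is reproduced to within 2 points.

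**2. Gain from baseline adjustment.** The article gives no prevalence, k or target effect for any secondary outcome, and no baseline–endline correlation. The retention inputs are therefore only a stand-in, the scale is a risk difference rather than the planned ratio, and the correlation r is assumed. Two cases bound the answer:

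- *Within only:* baseline values explain only the within-cluster part, which is 0.0277/0.0735 = 38% of the variance. The variance becomes 0.0277(1−r²) + 0.0458, with 28 df.
- *Both levels:* clinic-level prevalence persists equally strongly. The variance becomes 0.0735(1−r²), with 27 df.

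| r | 1−r² | Power, within only | Power, both levels | Standard error reduced by (within only / both levels) |
|---|---|---|---|---|
| 0 | 1 | 78.7% | 78.7% | – |
| 0.3 | 0.91 | 80.1% | 82.3% | 2% / 5% |
| 0.4 | 0.84 | 81.2% | 85.2% | 3% / 8% |
| 0.5 | 0.75 | 82.6% | 88.9% | 5% / 13% |
| 0.6 | 0.64 | 84.3% | 93.1% | 7% / 20% |

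For example, at r = 0.5 within only: 0.0277 × 0.75 + 0.0458 = 0.0666, and √(0.0666/15) = 0.0666. The gain runs from about 1 point (80.1 − 78.7) to about 14 points (93.1 − 78.7).

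**3. Size of an ordinary baseline difference.** Assume a prevalence of 30% and take 528/30 = 17.6 dyads per clinic at baseline. The SD of the chance difference between arms is √{(2/15)[0.3 × 0.7/17.6 + (k × 0.3)²]}. This is 4.6 points at k = 0.2 and 5.2 points at k = 0.3. If an imbalance of 1.96 SD occurred and endline prevalence followed baseline with an assumed slope of 0.3 to 0.5, it would leave about 3 points (0.3 × 1.96 × 4.6 = 2.7) to 5 points (0.5 × 1.96 × 5.2 = 5.1) in the unadjusted endline difference.

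**The case against.** The case against is substantial, and much of it stands.

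- **A reader might infer that depression, common mental disorder, hunger and adherence will all be compared unadjusted.** The article does not say so. These are scale scores without stated cut-offs, and the sentence applies only to outcomes that turn out to be binary. The one binary secondary definition given is viral load above 1000 copies per ml, for which no baseline measurement is described.
- **A reader might infer that the unadjusted ratio is biased.** Chance imbalance does not bias it over repeated randomisations. It adds variance, which the interval already reflects, and conditional error in the trial at hand. Only differential recruitment could bias it, and the article does not establish that this happened.
- **A reader might infer that the anticipated reduction in stress is affected.** In Table 2, parental stress is measured by the Parenting Stress Index, which the article does not describe as binary.
- **A reader might infer that adjustment is excluded.** The text does not forbid an adjusted estimate, and an SAP may add one. The adjustment sentence could even be read as general. But its lead covariate is baseline ELC, so the ELC reading is the natural one. Read generally, it would bring in caregiver mental health only if imbalanced, and never each outcome's own baseline value.
- **The trial was powered for ELC and retention only.** True; the point is therefore one of efficiency on secondary outcomes.

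What survives is that the article fixes a specific estimate, labels it unadjusted and treats ELC differently in the same paragraph. That is a stated choice rather than omitted detail.

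**Conclusion.** The point holds as a worthwhile improvement to a valid analysis, limited to secondary outcomes that are analysed as binary and also measured at baseline. For those, the named estimate discards information already collected and keeps any baseline difference between arms.

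The size is an assumption-dependent range and cannot be settled from the article. At r = 0.3 the benefit is small in either case (about 1 to 4 points of power). It becomes material only with stronger persistence, and the upper figures need clinic-level prevalence to persist as strongly as individual status does. The power figures illustrate the scale of the effect; they are not estimates for any particular secondary outcome.

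**What to change.** In Data analysis, state which secondary outcomes will be binary. For each one also measured at baseline, make the main estimate one adjusted for the participant's baseline value of that outcome and for stratum, by the two-stage cluster-level method:

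1. Fit an individual-level regression of the endline outcome on its baseline value and stratum, without trial arm.
2. Compute each cluster's observed-to-expected ratio (or residual) and compare arms by a t-test on these cluster values.

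Keep the unadjusted prevalence ratio as a supportive result. This preserves the plan's cluster-level approach. Trial status says analysis was ongoing at submission, so the change should be documented before arm comparisons of these outcomes are seen; if they have been seen, label the adjusted estimate as added afterwards.

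The cost is a few sentences, a little programming and a simple rule for missing baseline values, such as a missing indicator. No new data are needed.

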Many children in Sub-Saharan Africa face severe challenges affecting early development. Southern Africa has a generalised HIV epidemic. The current prevalence of HIV is estimated to be 14.6% among 15–64 year olds in Zimbabwe [24]. Despite notable reductions in the mother-to-child transmission rates, to 6.7%, at the population level [25], UNAIDS estimated that mother-to-child transmission is 6.39% [26]. The number of children orphaned due to AIDS is estimated as 524,581 [26]. High poverty (72% consumption poverty) with 25% of children living in extreme poverty [27] may also be a driver of poor child outcome.

Developmental challenges have been well documented in both HIV positive and HIV exposed infants [28–31]. The mechanisms are unclear. Exposure to the virus, antiretroviral (ART), or living in a family with HIV may all contribute, with the concomitant environmental risks associated with having parent(s) who are HIV-positive being one of the most influential factors among all those included. Effective interventions to mitigate these are available, and when implemented by the caregivers of HIV positive and HIV exposed children, it can improve their performance [12, 32, 33]. The intervention, we hypothesise, will result in improved long-term child development outcomes, reduced need for second and third line ART, reduced opportunistic infections and AIDS diagnoses and increased child survival (Fig. 1).

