### Sample size

Based on data collected in our pilot study, the mean Mullen ELC Score was 110.6 (standard deviation [SD] 16.1). The coefficient of variation (k) between clusters was 0.07 but this does not take account of the clustering effect of the group-based intervention so a value for k of 0.15 was used. Using these values, assuming a harmonic mean of 16 dyads enrolled per cluster and a loss to follow-up of 20%, 15 clusters per arm were needed to provide 80% power to detect an effect size (difference in means/SD) of 1.23 for the Mullen ELC Score. The same sample size provides 80% power to detect a risk difference of 20% in retention in care, assuming retention is 65% in the control arm and k = 0.2. Based on these calculations our recruitment target was 528 caregiver-child dyads in total from 30 clinics. We recruited 574 dyads to ensure a harmonic mean of 24 dyads was enrolled from the larger seven clinics and a harmonic mean of 12 dyads was enrolled from the smaller eight clinics. This was done to ensure ECS group sizes were sufficient to include 2 ISALS groups per ECS group.

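### The ratio of geometric mean clinic percentages cannot be computed for viral load in HIV-infected infants, and for retention it is paired with a test that needs to be made clear

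*Protocol article*

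**What the plan says.** The Data analysis section of the protocol article opts for cluster-level summaries because there are few clusters. It then groups child retention and unsuppressed viral load as HIV-specific primary outcomes, adds the binary secondary outcomes, and says that "the unadjusted prevalence ratio will be estimated as the ratio of the geometric mean percentage" between arms. The same sentence names logistic regression as the comparison. Individual-level logistic regression comes later, as a sensitivity analysis.

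Elsewhere in the article:

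- **Outcome measures and Table 2:** the infant viral load outcome (above 1000 copies/ml at 12 months) is restricted to HIV-infected infants and is secondary. The Abstract lists only cognitive development and retention as primary.
- **Background:** "Despite notable reductions in the mother-to-child transmission rates, to 6.7%, at the population level", next to a UNAIDS estimate of 6.39%.
- **Sample size:** "The same sample size provides 80% power to detect a risk difference of 20% in retention in care". The inputs are a control proportion of 65% and a between-cluster coefficient of variation k of 0.2. It plans on 16 dyads per cluster and 20% loss, and reports 574 dyads recruited.

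**The concern.** A geometric mean is zero as soon as one clinic is at 0%, because its log is then undefined. The arm ratio becomes zero or undefined. A clinic with no infected infant has no percentage to enter at all. With roughly one infected infant per clinic, both situations should be common. The plan would then prescribe an estimator for a named outcome that the data cannot supply, and some substitute would have to be chosen after the data are in.

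For retention the question is different. The trial was sized on an absolute risk difference, the effect is to be reported as a ratio of geometric means, and the test is called logistic regression. It is unclear whether that means a cluster-level or an individual-level analysis, and the stated 80% power belongs to neither scale by name.

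**Working it through.** **Infant viral load: inputs.** Children recruited: 574 in 30 clinics (Sample size). Share infected: 6.39% to 6.7% (Background), assumed as a proxy because the trial's own share is not given. Loss: 20% (Sample size). Unsuppressed rate: not given; 20% to 80% assumed. Clinic sizes of 12 or 24 come from the article, which gives two splits per arm: eight smaller and seven larger (Sample size), or six one-group and nine two-group (Randomisation process). Both were used. Infants are treated as independent; clustering of infection within clinics would leave more clinics empty.

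**Number infected.** 574 × 0.0639 = 36.7 and 574 × 0.067 = 38.5. After 20% loss: 29.3 to 30.8, or 0.98 to 1.03 per clinic.

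**Clinics with no infected infant.** P(none) = (1 − share)^m.
- Before loss, 6/9 split, 6.7%: 0.933^12 = 0.435 and 0.933^24 = 0.189, so 12 × 0.435 + 18 × 0.189 = 8.6 clinics. At 6.39%: 9.1.
- After loss, 8/7 split, about 10 or 19 analysed, 6.7%: 0.933^10 = 0.500 and 0.933^19 = 0.268, so 16 × 0.500 + 14 × 0.268 = 11.8 clinics. At 6.39%: 12.3.

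This gives about 9 to 12 of 30.

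**Clinics with none or 0% unsuppressed.** P = (1 − share × unsuppressed rate)^m, after loss, 8/7 split:

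| Unsuppressed rate (assumed) | Share of clinics empty or at 0% |
|---|---|
| 20% | 83% |
| 40% | 68% to 70% |
| 60% | 57% to 58% |
| 80% | 47% to 49% |

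The 6/9 split gives slightly lower shares (81% to 82% at a 20% rate, 44% to 46% at 80%).

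**Chance that all 30 clinics have a percentage above zero.** This is the product over clinics of 1 − P. After loss it is below 1 in a billion at a 60% unsuppressed rate and about 1 to 14 in a billion at 80%. With 15% infected and 60% unsuppressed it is still below 0.0001.

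**Dropping empty clinics.** The chance that no remaining clinic is at 0% is about 0.00002 to 0.00004 at a 40% unsuppressed rate, 0.003 at 60% and 0.08 at 80%.

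**Retention: the plan's own figure.** Alpha is assumed two-sided 0.05. With p0 = 0.65, p1 = 0.85, k = 0.2 and m = 16 × 0.8 = 12.8:

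c = 1 + (1.96 + 0.84)² × [p0(1−p0)/m + p1(1−p1)/m + k²(p0² + p1²)] / (p1−p0)²

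The bracket is 0.0735, so c = 15.4, and power with 15 clusters per arm is 78.8%. The stated 80% is reproduced to within about a point.

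**Retention: other tests.** The first, second, third, fifth and last rows are simulations with 15 clusters per arm; the fourth is the delta-method formula.

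| Assumption | Risk difference | Log percentages |
|---|---|---|
| k = 0.2 in both arms, beta clusters | 78.5% | 65.5% |
| k = 0.2 in both arms, logit-normal | 78.6% | 64.7% |
| Equal between-cluster SD of 0.13 | 85.6% | 78.9% |
| k = 0.2, delta-method formula | 78.8% | 77.7% |
| k = 0.1 | 96% | 94% |
| Truncated-normal clusters | 77% | 71% |

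The loss is about 1 to 14 points. An overdispersed logistic comparison has 75.5% power in the first setting, 3 points below the risk difference. Ordinary logistic regression that ignores clustering has a type I error of about 17% at k = 0.2. A clinic at 0% retention occurs in only about 1% to 3% of simulated trials.

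**The case against.** The strongest reply is that viral load would still be analysed. Logistic regression, named in the same sentence and again as a sensitivity analysis, accepts clinics at 0% and needs nothing from clinics without infected infants. That stands: a reader might infer that the viral load analysis yields no result, but what fails is the cluster-level ratio, not every comparison.

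A second reply is that handling of zeros belongs in a statistical analysis plan, and a zero count can be replaced by 0.5. That is fair for an occasional zero. It does not supply a percentage for a clinic with no infected infant, and with half or more of clinics empty or at 0% the estimate would largely reflect the substitution. The article also names this estimator itself, so the point concerns a stated rule.

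Third, the inputs are proxies. A transmission rate is not the trial's share infected, and the unsuppressed rate has no source in the article. A claim that most clinics are affected fails at about 80% unsuppressed. Non-computability does not depend on it, since one such clinic is enough.

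For retention, a reader might infer a fixed loss of about 13 points. The article does not support that: it names logistic regression, not a t-test on log percentages, and the 13 to 14 points need k = 0.2 in both arms with skewed cluster proportions. Reporting a ratio after sizing on a difference is not in itself an error.

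Finally, the primary label for viral load in Data analysis looks like a slip. That section itself later speaks of two primary outcomes.

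**Conclusion.** The point holds for infant viral load. On the article's own transmission figures, taken as a proxy for the share infected, the prescribed ratio cannot be computed: about 9 to 12 of 30 clinics would have no infected infant, and about half to five-sixths would be empty or at 0% for unsuppressed rates of 20% to 80%. The conclusion survives much higher infection shares. Its weight is that of a secondary outcome in about 37 to 38 infants, because the Abstract, Outcome measures and Table 2 all place viral load outside the primary outcomes.

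For retention the ratio is computable in nearly all trials and no fixed power loss is established. What remains is an unclear pairing of effect measure and test. The consequence ranges from a loss of about 1 to 14 points if log percentages are tested, through about 3 points for an overdispersed logistic comparison, to an inflated type I error if clustering is ignored.

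**What to change.** - **Infant viral load:** drop the ratio of geometric mean clinic percentages. Report counts and proportions pooled by arm. Compare arms with a method that respects clustering and tolerates empty or zero clinics, such as a cluster permutation test or a small-sample-corrected GEE, labelled exploratory.
- **Outcome label:** correct the Data analysis sentence so that viral load is secondary, in agreement with the Abstract, Outcome measures and Table 2.
- **Retention:** keep the ratio as a reported measure if wanted, but name one test that accounts for clustering. A test on cluster proportions is preferable because it matches the risk difference used for the sample size.

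The cost is wording; no data collection changes. The constraint is timing. Trial status reports that data analysis was already ongoing at submission, so the change should be dated and documented before outcomes are seen by arm. If they have been seen, it should be reported as a later change, since altering the analysis of a primary outcome then could look data-driven.
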